### Sample size

On average each renal unit in the UK has approximately 75 patients (range 20–250) active on the national kidney transplant waiting list [40]. The proportion of those listed who do not have a potential living-donor under assessment will be determined in this work. If 80% of those listed do not have a living donor under review, the eligible population at an ‘average’ site will be approximately 60 individuals. We will recruit from 2 centres, aiming for a target sample size of 60 patients (30 in each arm). This will allow us to estimate a recruitment rate of 50% with a 95% confidence interval of 41 to 59%. In the 60 randomised patients, we will be able to estimate a true rate of follow-up at 1 year of 70% with a 95% confidence interval of 58–82%.

### Data collection

Trial participants will have two standard study contacts and one optional qualitative contact:BaselineFollow-up: Questionnaire completion 1–3 days after the home visit or for those not receiving the intervention in the control arm, 4–8 weeks after the baseline assessment.Qualitative: After the home visit, some purposively sampled patient participants will be invited to consider participating in qualitative interviews.

Clinical and laboratory data will be extracted from hospital medical records by the research nurses. The data collected are reported in hospital medical records and do not require interpretation. Patient-reported outcome data will be collected through questionnaires self-completed by participants. Participant experience of the trial and intervention will be collected through qualitative interviews. Compliance with the intervention will be recorded by the intervention HCPs against a checklist.

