#### Intervention component 1: meeting between intervention HCP and transplant candidate — dedicated discussion about living-donor kidney transplantation and living kidney donation

The participant will meet with an intervention HCP within 2–4 weeks of recruitment. The first meeting should be undertaken in person, but if the participant requests it, the first meeting can be undertaken over the telephone or a virtual platform. The HCP will discuss living-donor kidney transplantation and living kidney donation with the participant. Participants will be informed about an educational animation video presenting an overview of living-donor kidney transplantation (adapted for UK use from animations developed by [name] Health Resources and Services Administration (HRSA) funded work in the USA [38]). The animation will be shown and links shared if the participant wishes. The HCP will ascertain the participant’s close relationships with relatives and friends and the estimated age, sex and health of these individuals. This information will be recorded and illustrated in a sociogram. No personal identifiers will be recorded in the sociogram. They will discuss the initial suitability of relatives and friends as potential living donors.

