#### Intervention component 3: home-based education and family engagement

The home visit will be undertaken by two intervention HCPs who will deliver the education and engagement package approximately 2–4 weeks after the first meeting. The home visit can take place at any day and time that suits the participant and their guests; this includes evenings and weekends. In exceptional cases, a second home visit may be required.

The home education and engagement session will cover the following: kidney disease (specific to the participant’s disease); dialysis; transplantation — deceased-donor and living-donor transplantation; living kidney donation; and open discussion.

The HCPs will share their work telephone number and work email addresses with participants so that they can be contacted for further advice and support if required at any time during the trial. If requested, a second home visit covering all or part of the content of the first visit can be delivered.

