### Outcomes

The primary and secondary outcomes and outcome measures are detailed in Table 1.

**Table 1 Tab1:** Primary and secondary outcomes and measures

	**Outcomes**	**Timepoint(s) of evaluation of outcome measures**
Primary	•Recruitment •Retention	•Recruitment at 0 week: % of those eligible and approached who consent to randomisation at invitation •Retention at 4–8 weeks: % completing follow-up questionnaire 4–8 weeks after baseline questionnaire

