Secondary	•Size of the eligible participant population •Participant and healthcare professional adherence to the intervention/trial •Fidelity of delivery of the intervention •Acceptability of the intervention and trial methods •Barriers and facilitators to intervention implementation in different settings •Estimates of the effect of the intervention on possible mediators of the intervention •Assessing linkage to UKRR data regarding planned outcome for later main trial (receipt of a LDKT) •Impact on existing healthcare delivery and potential for the intervention to become a normalised part of everyday care •Cost drivers	•Size of the eligible population screening at − 4 to 0 weeks •Adherence to intervention/trial and fidelity of delivery of the intervention assessed at 4–8 weeks — % of participants in intervention arm who receive the various intervention components; number of letters sent to potential donors per participant in intervention arm; % of participants who complete questionnaires at baseline and 4–8 weeks after baseline; number of protocol deviations reported; observed fidelity of intervention delivery •Acceptability of intervention and trial methods at 10 weeks — assessed through qualitative interviews •Barriers and facilitators to recruitment — measured by time to green light at each site and time to recruitment of first participant, assessment of screening log and qualitative interviews with participants, nonparticipants and healthcare professionals •Estimates of the effect of the intervention on possible mediators of the intervention at 4–8 weeks — measured through questionnaires measuring patient activation, social support, LDKT knowledge and health literacy at baseline and 4—8 weeks later • Assessing linkage to UKRR data regarding planned outcome for later main trial (receipt of a LDKT), assessed after closure of trial recruitment •Impact on existing healthcare delivery measured through qualitative interviews with HCPs after 3 months of study being active at study site • Cost drivers measured at feasibility trial completion

The primary outcome for the later full-scale RCT will be receipt of a LDKT. Secondary outcomes will include the number of potential donors undergoing assessment, the proportion of participants receiving a LDKT, participant patient activation, participant-perceived social support, participant transplant/donation knowledge and cost-effectiveness data.

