### Analytical methods

Analysis and reporting will be in line with the CONSORT (Consolidated Standards of Reporting Trials) extension for randomised pilot and feasibility trials [49]. Patient-reported outcome scores from questionnaire data will be calculated based on the developers’ scoring manuals, and missing and erroneous items will be handled according to these instructions. Continuous measures will be presented as means and standard deviations or medians and ranges depending on their distribution. Categorical data will be presented as frequencies and proportions, with 95% confidence intervals.

The study will assess the following primary outcomes:Recruitment: % of those eligible and approached who consent to randomisation at invitation.Retention: % completing follow-up questionnaire approximately 4–8 weeks after baseline questionnaire.

We will describe the primary outcome variables across socioeconomic position quantiles.

Descriptive statistics will be used to report the secondary outcomes of interest.

Qualitative interviews will be analysed using inductive thematic analysis, as described by Braun and Clarke[50]. Transcripts will be read twice to gain familiarisation and sections of text coded by assigning descriptive labels. Codes will be grouped based on shared properties and themes identified. All transcripts will be independently coded by two researchers, the CI and another qualitative researcher. Codes will be discussed to maximise rigour and reliability, to identify areas of discrepancy and to refine the coding system. NVivo software will be used to aid analysis. Data collection and analysis will be conducted concurrently, employing an iterative approach. The sample size for the qualitative phase will be determined by reaching theoretical theme saturation [51].

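### Follow-up questionnaire timing differs by arm and conflicts with the single 4–8 week window that defines retention and the mediator timepoint; missed, late or repeated home visits could distort both

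*Protocol article*

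**What the plan says.** **Trigger.** The Data collection section sets the follow-up contact as "Questionnaire completion 1–3 days after the home visit or for those not receiving the intervention in the control arm", "4–8 weeks after the baseline assessment". The first rule depends on an event and the second on elapsed time.

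**Definition of the outcomes.** Table 1 defines the primary outcome as "Retention at 4–8 weeks: % completing follow-up questionnaire 4–8 weeks after baseline questionnaire". Analytical methods repeats it with a softener: "Retention: % completing follow-up questionnaire approximately 4–8 weeks after baseline questionnaire". Table 1 also lists "Estimates of the effect of the intervention on possible mediators of the intervention at 4–8 weeks", and Table 3 puts all patient-reported measures at 4–8 weeks in a column headed as time after baseline. None of these places distinguishes the arms.

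**Timing of the visit.** For component 1: "The participant will meet with an intervention HCP within 2–4 weeks of recruitment". For component 3, the home visit comes "approximately 2–4 weeks after the first meeting". A second home visit is allowed.

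**Participants who do not follow their allocation.** The Follow-up data section lets people who withdraw from treatment stay in follow-up. The process evaluation section speaks of attempts to collect patient-reported data from participants who are noncompliant with their arm.

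**The concern.** Retention is one of two primary outcomes. It is meant to show whether randomised participants can be followed up, and it will be described across socioeconomic position. Receipt of the intervention components is a separate secondary outcome. If the questionnaire in one arm is released by the home visit, the two can run together: a missed visit may appear as a missing questionnaire, and a late visit as a questionnaire outside the window.

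The Data collection sentence leaves three cases open:

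- an intervention-arm participant who has no home visit;
- a visit that takes place after week 8;
- two visits, where it is not said which one starts the 1–3 day clock.

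The phrase about those not receiving the intervention in the control arm is itself unclear. It could mean controls only, or anyone without the intervention.

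The mediators raise a separate issue that does not depend on slippage. Transplant knowledge, patient activation, social support and health literacy would be measured 1–3 days after an education session in one arm, and at a time unrelated to any session in the other. Knowledge, activation and social support are planned secondary outcomes of the full trial, so the estimates obtained here may shape its design.

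**Working it through.** **1. The plan's own precision figure.** The Sample size section gives 70% follow-up in 60 patients with a 95% interval of 58–82%. The Wald half-width is 1.96 × √(0.70 × 0.30 / 60) = 0.116, giving 58.4% to 81.6%. The figure reproduces. It is labelled as follow-up at 1 year, so 70% is used below only as a planning rate.

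**2. On-schedule timing.** Take recruitment and baseline as the same day (an assumption).

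| Step (intervention arm) | Earliest, days | Latest, days |
|---|---|---|
| First meeting after recruitment | 14 | 28 |
| Home visit after first meeting | 14 | 28 |
| Questionnaire after home visit | 1 | 3 |
| **Total after baseline** | **29** | **59** |
| Control arm window | 28 | 56 |

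The overrun is at most 59 − 56 = 3 days.

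To see how often it would occur, suppose the three intervals are independent and uniform over their ranges. The total exceeds 56 days when the combined shortfall of the first two intervals from 28 days each is smaller than the last interval, u. That probability is E(u²) / (2 × 14²). For u uniform on 1 to 3, E(u²) = (27 − 1)/6 = 4.33, so the probability is 4.33/392 = 1.1%.

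**3. What missed or late visits could do to retention.** The documents give no rate for these. As an illustration, let a share q of the intervention arm yield no questionnaire inside the window because the visit was missed or late, and let everyone else respond at 70%.

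Intervention-arm retention = 0.70 × (1 − q). Pooled retention (1:1) = [0.70 × (1 − q) + 0.70] / 2.

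| q | Intervention arm | Pooled | Gap between arms |
|---|---|---|---|
| 0 | 70% | 70% | 0 points |
| 10% | 63% | 66.5% | −7 points |
| 20% | 56% | 63% | −14 points |
| 30% | 49% | 59.5% | −21 points |

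At q = 20% (6 of 30 participants) the pooled figure falls by 7 points, against a planned half-width of 11.6 points. If those participants are instead sent the questionnaire at 4–8 weeks and respond at 70% like the rest, every row returns to 70%.

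**4. Mediators.** The interval from teaching to measurement is 1–3 days in the intervention arm by design. No such interval exists for controls. The documents give no figures on how quickly scores fade, so the size of any distortion cannot be calculated.

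**The case against.** The strongest reply is that the protocol already has a default timepoint. Tables 1 and 3 and Analytical methods all give 4–8 weeks after baseline without regard to arm. People who withdraw from treatment may continue follow-up, and questionnaires are sought from non-compliers. The two triggers look chosen to coincide, and on schedule they nearly do. Both the retention definition in Analytical methods and the home-visit interval are qualified as approximate, so a day-59 questionnaire need not be rejected. Retention is a descriptive percentage and not a comparison of arms, mediators are reported descriptively, and the Access to data section says the study was not designed for meaningful analysis of quantitative outcomes. Measuring soon after an intervention is also a legitimate way to see whether its targets move at all. Figure 1, to which the text refers for timings, is not shown.

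Most of this stands, and it limits the point. A reader might infer that unvisited participants have no follow-up and are counted as not retained; the provisions for withdrawal and noncompliance do not support that. A reader might also infer that many questionnaires will be late. Adding an exponential delay with a mean of 7 or 14 days to the timing model above does put about 25% or 46% beyond day 56. Those delays are invented, however, and the result also needs a hard cut-off that Analytical methods does not impose.

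What the reply does not remove is the conflict itself. One section ties the intervention-arm questionnaire to the visit, while the outcome definitions tie it to baseline. Follow-up of unvisited participants is evidently intended, but the Data collection sentence sets no time for it.

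**Conclusion.** The inconsistency is real and concerns how a primary outcome is measured. The documents support saying that it can distort retention, not that it does so. On schedule the timing difference is at most 3 days and affects about 1% of intervention-arm questionnaires, assuming uniform intervals. With missed, late or repeated visits, retention in that arm could be understated by an unknown amount. The illustrated 7- to 21-point gaps rest on assumed rates of 10–30% and on no in-window response from those participants; the effect is zero if they are followed up at 4–8 weeks and respond like the rest.

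The mediator point holds whether or not visits slip: scores within 3 days of teaching are set against scores tied to no session. A reader might infer that the estimates will overstate a lasting effect. The protocol claims no lasting effect and analyses these measures descriptively, so the supportable statement is that a difference may reflect immediate recall.

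**What to change.** Bring the Data collection section into line with Tables 1 and 3:

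- Use one trigger in both arms, counted from baseline and placed late in the existing 4–8 week window, for example week 8 with a small stated tolerance.
- Send the questionnaire whether or not a home visit has taken place, and however many visits there have been.
- Count retention over all randomised participants and report it by arm as well as overall.
- Record the home-visit date so that days from visit to questionnaire can be described beside the mediator scores.

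The trigger should stay within 4–8 weeks. Moving it to, say, 8–10 weeks would redefine the primary outcome.

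The cost is revised wording and a changed data-capture trigger; the stated retention precision (58–82%) is unaffected. The small downside is that a few late home visits will fall after the questionnaire, and knowledge will be measured somewhat longer after teaching.

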#### Baseline data

Demographic, social, clinical and patient reported data will be collected by research nurses at the baseline visit (following consent and prior to randomisation) (Table 2). No blood or urine tests are required other than those that are being performed as part of routine care.

**Table 2 Tab2:** Summary of baseline data collection for the feasibility randomised controlled trial

Demographics	Age, sex, ethnicity, religion, marital status + / − children, employment status, education level, housing tenure, EIMD 2019 score, distances lived from kidney hospital and transplanting hospital, car ownership, alcohol consumption, smoking history
Clinical	Primary renal disease, date of current transplant listing, comorbidities, current stage of kidney disease (pre-emptive, haemodialysis, peritoneal dialysis), body mass index (BMI)
Patient reported	Renal and transplant knowledge (R3K-T [41]), social support (ISEL-12 [42, 43]), patient activation (PAM13 [26, 44]), health literacy (SILS [45, 46]), transplant preference, transplant beliefs [47], experience talking to family and friends about kidney disease and living donation (binary response questions), quality of life (EQ-5D-5L [48])
Laboratory	Blood group, tissue type at HLA-A, B and DR, matchability (levels 1–10), % calculated reaction frequency
Family and social network	Draw sociogram/social network diagram — containing information on all close relationships with relatives and friends and the estimated age, sex and health of these social contacts

#### Follow-up data

Figure 1 outlines the planned data collection timepoints. Data will be entered directly onto online electronic case report forms (eCRF) and patient participant questionnaires (Table 3).

**Table 3 Tab3:** Summary of follow-up data collection for the feasibility randomised controlled trial

		Time after baseline
Clinical	Current transplant listing status (active, suspended, removed, transplanted. If transplanted, the date and type of transplant will be recorded), comorbidities, current stage of kidney disease (pre-emptive, haemodialysis, peritoneal dialysis), date of death (if this has occurred), cause of death (if this has occurred), BMI	12 weeks
Laboratory	Matchability, % calculated reaction frequency	12 weeks
Resource use	Number of donors undergoing assessment	12 weeks
Compliance with and acceptability of trial	Number of living donation letters posted to potential donors; number of home visits by intervention healthcare professional (HCP); content compliance (quantitative checklist for home visit content)	4–8 weeks
Patient reported	Renal and transplant knowledge (R3K-T [41]); social support (ISEL-12 [42, 43]); Patient Activation (PAM13 [26, 44]); health literacy (SILS [45, 46]); transplant preference; transplant beliefs [47]; experience talking to family and friends about kidney disease and living donation (binary response questions); quality of life (EQ-5D-5L [48])	4–8 weeks

Standardised tools are being used as follows:Demographics: EIMD 2019 score [37].Patient-reported mediator and outcome measures: Renal and transplant knowledge (R3K-T) [41], social support (ISEL-12) [42, 43], patient activation (PAM13) [26, 44], health literacy (SILS) [45, 46], transplant preference, transplant beliefs [47], experience talking to family and friends about kidney disease and living donation (binary response questions) and quality of life (EQ-5D-5L [48]).

Participants who have been recruited to the trial can choose to withdraw from their allocated treatment. If they withdraw from treatment, they can continue to consent to follow-up assessments or withdraw from both treatment and follow-up assessments. Data already collected will be kept, and clinical outcomes from hospital records and UKRR and NHS blood and transplant registries will be extracted if the participant has consented to this. Participants who withdraw from follow-up assessments will have no further contact from the research team regarding the trial.

#### Outcome data

At the point of consenting to take part in the RCT, all participants will be asked to consent to linkage to existing healthcare databases held by the UKRR and NHS Blood and Transplant. These databases can provide data on commencement of kidney replacement therapy, date and type of kidney transplant, date and cause of death, if this information is missing from the medical records. This will enable follow-up of clinical outcomes for participants who lose capacity to continue providing consent or are lost to follow-up, including those who move to a renal unit not participating in the trial.

### Mixed-methods process evaluation

A process evaluation will be used to study how the intervention is implemented and may provide information on contextual factors that affect the intervention. It will also provide information about the uniformity of delivery of the intervention to different participants in different locations, where the ‘same’ intervention may be delivered and received in different ways. The integrated qualitative research will provide a more in-depth understanding of how the trial treatments and procedures are being delivered and received in practice.

Process evaluation will be undertaken by the chief investigator (CI) and research nurses using the following mixed methods:Semi-structured qualitative interviews with participant and non-participant transplant candidates and family members to understand experience and acceptability of intervention and with practitioners on experiences of deliveryMixed-methods observations of at least two home visits at each study site, assessing fidelity of delivery against a quantitative checklist and making qualitative observation field notesQuantitative data collection regarding patient participation aggregate data from participating sites on eligible population and invited population, including % of those eligible who were invited to participate and % of those invited who agreed to participation, were recruited

Fidelity of delivery of the first meeting part of the intervention will be assessed using implementer self-report against a structured checklist and qualitative interviews with participants and implementers. Fidelity of the home visits will be assessed through structured observations with a quantitative checklist, qualitative observation notes and participant and implementer qualitative interviews.

Process information will be documented in the compliance log. For participants in the intervention arm, the research nurse, an intervention HCP or CI will use the quantitative intervention delivery checklist, recording the delivery of components of the intervention. For participants in the control, arm compliance will be recorded at the end of the study by the research nurse recording whether the participant received any elements of the intervention from another source. We will explore the reason for not complying with treatment as recorded in the compliance log and investigated through qualitative interviews. If participants who are noncompliant with their allocated treatment arm do not respond to attempts to collect patient-reported outcome data, outcome data that can be extracted from medical records and national registries will be used.

Qualitative interviews will be used to investigate the following:i)**Reasons for nonparticipation:** Individuals who decline to participate in the trial will be asked if they will be willing to explain why they do not wish to participate, over a telephone interview.ii)**Experience of the intervention and trial:** Following delivery of the intervention (clinical invitation letters to family and friends and the home education and engagement session), patient participants, family and friends present at the home visit and practitioners will be invited to an in-depth qualitative interview which can be undertaken in person or over the telephone. These interviews will investigate the acceptability of both the intervention and trial methods and will be used to investigate ways of tailoring and optimising the intervention resources for future trials. Participants will be purposively sampled aiming for diversity in age, sex, ethnicity, socioeconomic status and primary renal disease. Participation in the qualitative interviews is optional.

Example interview topic guides are provided as supplemental material.

